#### Health effects

The difference in the cumulative incidence of depression at 18 months will be measured as stated in the paragraph described above (‘main outcome’). Quality Adjusted Life Years. (QALYs) will be measured using the EuroQol-5D. Spanish tariffs will be used to estimate the utility of health states described by the patients [91,92]. QALYs will be calculated by multiplying the utility by the amount of time a patient spent in a particular health state. Linear interpolation will be used for transitions between health states. QALYs will be assessed at baseline, 6, 12 and 18 months.

#### Cost effectiveness and cost-utility analysis

As in the effectiveness analyses, we will take two approaches to the cost-effectiveness and cost-utility analyses: 1) a complete case analysis with covariate adjustment and 2) an analysis after multiple imputations with covariate adjustment. For the first strategy we will apply the inverse probability weighting to the final model. We will calculate incremental cost-effectiveness ratios (ICER), which are calculated as incremental cost (mean cost for intervention group minus mean cost for control group) divided by incremental effectiveness (mean effect for intervention group minus mean effect for control group) [93]. Incremental cost-utility ratios (ICUR) will be calculated in the same way. The only difference is that the effect will be the difference in QALYs. The incremental costs and incremental health effects will be modeled by generalized linear models (GLM). The modified Parks test will be used in order to select the appropriate family. In order to identify the correct link function we will compare model performance of all permutations of candidate link and variance function using different diagnostic tests such as the Pregibon Link test, the Hosmer-Lemoshow test and the Copas test [93]. We will check the intraclass correlation coefficients and the likelihood-ratio tests with health center, FP and both as we said before. If the clustering effect is relevant, we will use robust standard errors for the cluster indicated.

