#### Inverse probability weighting

For each patient the probability of remaining in the follow-up at 18 months will be obtained through a logistic regression model (multilevel if appropriate) with the variable ‘remaining in the follow-up’ (yes/no) as dependent variable and a set of predictor variables measured at baseline. For the effectiveness analyses with complete cases we will apply the inverse probability weighting to the final model to adjust for a possible attrition bias due to participants lost during the follow-up [84,85], implemented through the ‘GLLAMM’ program [86].

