### Economic evaluation

The Economic Evaluation will be presented from two perspectives: 1) a Societal Perspective, including the costs of all types of health services (direct costs) and the costs that stem from production losses (indirect costs); and 2) Health System (including only direct costs). Although NICE [87] recommends just performing economic evaluations from the Health System perspective, we will present both due to the major impact that depression has on productivity [6,88,89]. The time frame of this study will be 18 months. Therefore, we will discount both costs and effects at 3.5% following NICE recommendations [87]. All costs will be expressed in euros (€) for the reference year 2012.

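### The weights for the complete-case cost and QALY analyses model presence at 18 months, not possession of all the data those analyses need

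*Protocol article*

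**What the plan says.** The section *Inverse probability weighting* of the protocol article defines one weight model: "For each patient the probability of remaining in the follow-up at 18 months will be obtained through a logistic regression model". Its dependent variable is a single yes/no indicator and its regressors are "a set of predictor variables measured at baseline". The stated purpose is "to adjust for a possible attrition bias due to participants lost during the follow-up".

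The section *Cost effectiveness and cost-utility analysis* carries this over: "As in the effectiveness analyses, we will take two approaches to the cost-effectiveness and cost-utility analyses". These are a complete-case analysis and an analysis after multiple imputation, both with covariate adjustment. Of the complete-case analysis it says: "For the first strategy we will apply the inverse probability weighting to the final model". No other response model is described.

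The data needed are set out elsewhere. Under *Health effects*: "QALYs will be assessed at baseline, 6, 12 and 18 months" and "Linear interpolation will be used for transitions between health states". Under *Economic evaluation*: "The time frame of this study will be 18 months". The *Cost* section names a modified CSRI without giving its waves or recall window. *Follow-up* has the questionnaires administered at all four evaluations.

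**The concern.** Inverse probability weighting removes selection only if the modelled event is entry into the analysed set. Here two events are in play. The weight model describes being present at the last visit. The QALY complete-case set consists of patients with a usable EuroQol at every wave. A patient who misses month 6 or 12 and returns at 18, or who attends throughout but leaves a EuroQol or cost item blank, is a success in the first and is excluded from the second.

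If such patients differ from the others, the complete-case ICER and ICUR keep that selection while being presented as adjusted for attrition. The weighted complete-case analysis also becomes a weaker check on the imputed one. The issue is which event is modelled, not which predictors are used.

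**Working it through.** No figure in the plan bears on this point, so there is none to reproduce. The check compares the two events and then illustrates the consequence with assumed inputs.

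**1. The two events.** Let p(x) be the probability of being present at 18 months given baseline x. Let q(x) be the probability of having all the other needed data, given presence at 18 months. Complete QALY cases are selected with probability p(x)q(x). The planned weight is 1/p(x), so a factor q(x) remains. If missingness depends on x only, the bias in an arm mean of Y is

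Cov(q, Y) / E(q).

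This is zero if q = 1 (monotone dropout, no item gaps) or if q is unrelated to Y.

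**2. How far the sets can diverge.** The article plans 1643 patients per arm and gives no retention rate. Complete cases per arm are 1643 × retention × (1 − interim gap):

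| Assumed 18-month retention | No interim gaps | 5% | 10% | 15% |
|---|---|---|---|---|
| 70% | 1150 | 1093 | 1035 | 978 |
| 80% | 1314 | 1249 | 1183 | 1117 |
| 90% | 1479 | 1405 | 1331 | 1257 |

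The two sets coincide only in the first column.

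**3. Effect on the QALY difference.** All inputs are assumed: one third of patients at high risk; retention 70% (high risk) and 82% (others); mean utility 0.70 and 0.85; true gain 0.020 QALY. The true control mean is 1.5 × (0.70/3 + 0.85 × 2/3) = 1.200. Presence at 18 months is 0.70/3 + 0.82 × 2/3 = 78.0%.

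- *Monotone dropout.* q = 1, so both sets of weights agree and the gain is 0.020.
- *Interim completeness 85% (high risk) and 95% (others), same in both arms.* Patients with all waves: 0.70 × 0.85/3 + 0.82 × 0.95 × 2/3 = 71.8%. E(q) = 0.9167 and Cov(q, Y) = 1.105 − 0.9167 × 1.2 = 0.005, so each arm mean is too high by 0.005/0.9167 = 0.0055. The control mean becomes 1.205, but the gain stays at 0.020.
- *Interim completeness in high-risk patients 90% (control) and 75% (intervention), others 95%.* Control bias: (1.1225 − 0.9333 × 1.2)/0.9333 = 0.0027. Intervention bias: (1.070 − 0.8833 × 1.2)/0.8833 = 0.0113. The unadjusted gain is 0.020 + 0.0113 − 0.0027 = 0.029. Weights for having all waves return 0.020.

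A simulation of 2,000,000 patients agreed to within sampling error. In the third case, once the risk variable that drives missingness was adjusted for, the gain was 0.020 with either set of weights.

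**The case against.** Several objections have force.

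- *Monotone missingness.* If nobody who misses an interim visit returns and no items are blank, or if remaining in follow-up is taken to mean without any gap, the events are the same. The article settles neither. Its exclusion criteria remove only patients expecting to be out of the city for more than four months, so shorter absences that overlap a 6- or 12-month visit are possible. Item gaps can occur even with monotone attendance. The objection makes the point conditional; it does not remove it.
- *Condensed article.* Definitions of the complete case may sit in a fuller document. But the article itself names the dependent variable of the weight model and reuses the weighting. The mismatch is therefore in a stated rule, not in an omitted detail.
- *Costs.* The need for every cost report is inferred from the 18-month horizon and the visit schedule, because the CSRI recall window is not given. This stands; the QALY argument does not depend on it.
- *Covariate adjustment.* Both strategies are adjusted, and the third illustration shows that adjustment can remove the whole bias when the driver of missingness is in the outcome model. This stands and limits the likely size.

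A reader might infer that interim missingness goes uncorrected throughout the economic evaluation, including the cost-effectiveness planes and acceptability curves. The documents do not support that. Multiple imputation is the parallel strategy and can use the observed waves of a patient with a gap. *Quantification of uncertainty* runs the bootstrap on each imputed dataset, and the planes and curves are drawn from those bootstrapped pairs.

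**Conclusion.** The point holds in a limited form. As written, the weights for the complete-case economic analyses target presence at 18 months, while the QALY analysis selects on all four waves. Unless missingness is strictly monotone with no item gaps, the weights do not match entry into the analysed set. The complete-case ICER and ICUR can then keep selection from interim missingness that covariate adjustment does not absorb.

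The size cannot be derived from the document. The illustrated shift of about 0.009 QALY needs interim missingness that differs by arm, is related to utility, and is driven by a variable left out of the outcome model. Equal interim missingness in the two arms gave no bias in the difference. A reader might be tempted to conclude that the bias rivals the intervention's whole QALY benefit. That would rest entirely on assumed rates and an assumed QALY loss per case, none of which the article gives.

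**What to change.** In *Cost effectiveness and cost-utility analysis*, state that the dependent variable of the weight model is having all the EuroQol scores and cost reports that the analysis needs, instead of remaining in follow-up at 18 months. Use one common set of complete patients and one set of weights for the paired cost and effect differences, so that numerator and denominator of each ratio describe the same patients. If the investigators expect no interim or item gaps, they could instead state and justify that assumption.

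The cost is one or two extra logistic models, a sentence of text and slightly more variable weights. The change corrects only the part of the selection that the baseline predictors explain, so the imputation analysis is still needed beside it.

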#### Quantification of uncertainty

To estimate the uncertainty around the ICER and ICUR, we will calculate 95% confidence intervals around the mean cost differences using the non-parametric confidence interval. Bootstrapping with 5000 replications will be performed on each imputed dataset [93,94].

#### Generation of cost-effectiveness planes and cost-effectiveness acceptability curves

Bootstrapped cost effect pairs will then be plotted on cost effectiveness planes and used to estimate cost effectiveness acceptability curves (CEACs). In the cost-effectiveness planes the ‘x’ axis represents the difference in effects and the ‘y’ axis the difference in costs. CEACs show the probability that a treatment is cost effective at a specific ceiling ratio, which is the amount of money society is willing to pay to gain one extra unit of effect. Willingness to pay values will range from 0€ to 100,000€ [95].

#### Sensitivity analyses

A number of sensitivity analyses will be conducted in order to assess the robustness of the results. Among others, these analyses will include: modification of the unit cost of different values such as primary care physician visits or nurse practitioner; modification of discount rates (from 0% to 6% as NICE recommends); modification of the cost for absenteeism (using the mean salary instead of the minimum); and modification of the cost including loss of productivity by presenteeism.

## Intervention

The new intervention will be applied at patient level by the FPs in the intervention group. This intervention will be tailored to each patient based on his/her risk profile of depression (risk factors present) and his/her risk level (likelihood of becoming depressed at 12 months), and it will be built up from a total of 5 components, which may act both independently and interdependently [96]:

**Figure 1 F1:**
[figure not shown]
Example of the mechanisms to reduce the likelihood of becoming depressed after the intervention to prevent the onset of depression by the family physician.

1) *Training workshop for family physicians in the intervention group*

A qualitative research study conducted prior to this RCT [97] found that FPs were resistant to informing their patients about their risk of depression, and also raised doubts about the validity of the predictD risk algorithm. FPs said they had little training on prevention of depression, and expressed uncertainties about what they should advise their patients. They were also fearful about the possible distress that could result in patients being informed of their risk for depression and commented on the lack of time for these preventive activities. Accordingly, the FPs will receive a 10–15 hour training workshop during working hours in the new intervention. This will enable them: 1) to interpret and make a specific and global evaluation of the risk for depression for each patient; 2) to transmit this information to the patient in an understandable and comprehensible way, without causing alarm; 3) to undertake active listening to patients about their beliefs, expectations and impact on information transmitted; 4) to provide tailored advice for each patient depending on his/her set of modifiable risk factors for depression; 5) to be able to integrate and personalize advice to give each patient based on his/her health history, previous doctor-patient relationship and bio-psycho-family-social circumstances; 6) to support those patients excessively worried by the information given. In the workshop we will use role-playing and video comments in groups in order to discuss and practice with FPs how to deal with different situations. The educational units, that we will use, are shown in Additional file 1: Annex 1. Previously, we will “train the trainers” to ensure that the training of the FPs will be performed to a minimum standard of quality and in standardized manner in each of the cities participating in the study.

2) *Communicating the level and risk profile of depression*

How patients are informed about their risk of becoming ill (cardiovascular events, hip fractures…) determines the outcome of prevention efforts [98,99]. In the same qualitative study as mentioned above, we found that primary care patients are pleased to be informed of their risk for depression [97]. Communicating with patients about their level and risk profile for depression is very new as until now there have been no validated risk algorithms to predict its onset [33,34]. This is also “*the starting component*”, which will activate the other components of the intervention. Each FP will receive (at baseline, 6 and 12 months) a report with the information on risk from each of 24 patients not depressed at baseline (belonging to their usual patient list) who will be randomly selected and will provide informed consent to participate in the study. This report will include the likelihood of becoming depressed at 12 months and the patients’ responses to each of the risk factors included in the predictD-Spain equation [34]. An example of a report of a patient who has 24.4% of becoming depressed at 12 months is shown in Figure 1.

If a patient has a moderate or high risk level (2nd or 3rd tertile), the FP will arrange an appointment with the patient aiming to communicate his/her risk of depression. If a patient has a low risk (1st tertile), the FP will have the option to report by telephone or face to face depending on the patient’s preferences. If a visit is scheduled, this will last approximately 10 minutes. This process of transmitting risk information will be held at baseline, 6 and 12 months. Reports will not include information about major depression diagnosis by CIDI at 6 and 12 months; although we will recommend that FPs screen for depression if the risk of depression was moderate or high at 6 and 12 months. FPs will write down on the problem list (clinical chart) the label “*predictD*” in order to remind them on opening their clinical charts that patients are included in the program predictD to prevent depression. This will help to ensure that when patients see their FPs, regardless of the reason for the consultation, doctors will take into account the information on their risk of depression if applicable.

3) *Building up a tailored bio-psycho-family-social intervention to prevent depression by family physicians*

Unlike psychosocial interventions developed to date to prevent depression, our intervention will be provided by FPs. With this approach we intend to draw on and integrate those usual components of primary care that could converge in the prevention of depression:

1. Previous knowledge and doctor-patient relationship: Family physician’s commitment to the patient has no defined end point. This continuity of the relationship and attention over time helps FPs to acquire a comprehensive understanding of the health problems, illness behavior, coping style, cultural background, and family and social context of their patients. Moreover, most patients will develop trusting relationship with their FPs. Patients will feel free to expose personal aspects of their lives in order to receive help, and FPs will need less time to know and understand particular aspects of any situation.

1. Establishment of a basic psychotherapeutic relationship: Many patients already consider FPs to be their primary source of mental care [100], although many FPs are not aware of this. Patients expressed this idea when asked about who would be the most appropriate person to communicate their risk of depression [97]. An interview in which a FP tries to communicate adequately to the patient his/her level and risk profile of depression will encourage the patient to express his/her concerns about the circumstances and problems that, in his/her opinion, could precipitate depression. FPs will then actively listen and offer an emphatic response, gathering additional and relevant information where needed and giving any advice if appropriate. The patient and the FP could agree to schedule a new visit to continue talking about preventing depression, but the only mandatory visits that FPs will arrange are those to report the risk of depression at baseline, 6 and 12 months. These are not psychiatric interviews or formal psychotherapeutic interventions, but may give the opportunity for the patient to feel heard and understood from a cognitive and emotional standpoint [101]. It is also intended to help the patient to be activated and empowered.

1. Family-oriented practice: FPs often bring a family orientation to bear in their clinical practice [102]. It has been reported that there are up to 5 levels of family-centered medical care in primary care [103]. We believe that the FP in our study are at the third level: FPs take an active interest in the feelings and concerns of the family in an empathic way. Family-oriented practice should be understood from the system theory, so that a change in any element of the family system could prevent depression in the patient. For example, a FP could help to improve the quality of life of a person who has the responsibility of caring for a relative with Alzheimer’s Disease and this may prevent depression [28]. This is feasible because in Spain members of the same family usually share the same FP. Primary care patients think it is useful to involve the family and consider the family resources and the possibility of involving other family members in coping with the risk of depression [97].

1. Social prescribing and community referral by FPs: Many social and personal problems cannot be dealt with effectively by the FP and require community resources [104]. The social dimension of the practice of primary care is the least accepted by FPs [105] and little is known about the effect on health of social prescribing and community referral by the FP. However, we will encourage FPs in the intervention group to become familiar with the community resources in their area. We will advise them on using centers. Moreover, we will advise them on using social prescribing in patients deemed appropriate with the aim of preventing depression. Primary care patients suggested participation in informal support groups to help them restructure their lives [97].

1. Management of physical problems: some physical problems are considered risk factors for depression, such as serious diseases (cancer, heart attack, stroke, …) [20,24], disabling illness (blindness, deafness, arthritis, …) [26] and/or chronic health problems (diabetes, chronic pain, …) [25]. Moreover, in our predictD studies [33,34] poor physical quality of life was an important predictor of depression, and FPs will receive this information in the patient’s reports. Therefore, appropriate management of physical problems could also help prevent depression.

4) *Offering a booklet to prevent depression*

At the first intervention visit, at baseline, FPs will give patients a brief booklet (a diptych) with advice for preventing depression (Additional file 1: Annex 2).This booklet is based on the recommendations on health promotion and preventive activities of the " Spanish Family and Community Medicine Society", in its section on mental health (PAPPS) [106]. At the end of this booklet reference is made to three websites with information for patients and relatives about depression, anxiety and insomnia [107].

5) *Activating and empowering patients*

People have favorable attitudes and beliefs about prevention of depression that do not conflict with evidence-based programs [100,108]. Activating and empowering patients to act on this knowledge might lead to an increased perception of self-efficacy, which is the gateway to changing attitudes and behavior to prevent depression. Primary care patients are in favor of receiving information about their risk for depression from their FP but seeking solutions themselves, with or without the help of the FP [97]. We will encourage FPs to invite patients to make suggestions during the interview on strategies, attitudes and behaviors they are already using to prevent depression. FPs will then positively reinforce those that in their opinion are the most appropriate to prevent depression for each patient.

### Explanatory model for the prevention of depression in primary care

Figure 2 shows the theoretical model that integrates the five components of the intervention to prevent depression from primary care: There are patient’s internal risk factors (sex, age, gene, personality, etc.) and external factors (threatening events) that can trigger an episode of major depression, depending on internal (coping style) and external (family and social support) resources that might be activated. Firstly, we introduce in the system “the training workshop” for FPs (*component 1*) to improve their knowledge, attitudes and skills to prevent depression with the new intervention. The FP usually has previous knowledge and a doctor-patient relationship (*component 3.1*) that generally predisposes toward a better intervention to prevent depression by both doctor and patient. We will give FPs risk information from patients, which they will use to communicate their level and profile of risk of depression (*component 2*). This is the “starting component” that will activate the rest of the components, creating a new doctor-patient interaction, whose essential element is the establishment of a basic psychotherapeutic relationship (*component 3.2*). The family-oriented practice (*component 3.3*), social prescribing and community referral (*component 3.4*), and management of physical problems (*component 3.5*) might be activated or not depending on the risk factors of depression involved in each patient, the FP’s skills, and the patient’s preferences. In all cases, FPs should provide the booklet to prevent depression (*component 4*), although the patient may or may not decide to use it. Finally, the FPs, taking into account the above components, will encourage their patients to speak about those strategies, attitudes and behavior they are already doing to prevent depression, in order to achieve their activation and empowerment (*component 5*). Thus, the patients can improve their perception of self-efficacy, which in turn promotes changes in attitudes and behaviors to prevent depression. There are also internal (sex, personality, psychosocial and preventive orientation, etc.) and external (work stress, team support, etc.) factors in the doctors that may influence their ability to conduct a successful intervention. The differences between interventions to prevent depression conducted so far in adults and the new intervention that we propose in primary care are summarized in Table 2. An example of how the intervention can lead to a reduced risk for depression is shown in Figure 1, and another example on the doctor-patient interview to prevent depression can be seen in a video (Additional file 1: Annex 3).
